**Figure 4 fig4:**
[figure not shown]
Display of step reaction time test.

###### Selective attention

2.4.2.1.3

The Go/No-Go test will be conducted using the Dividat Senso and it measures selective attention and inhibition (40). Participants fixate on a small grey dot in the middle of the screen. Crosses (+) and Xs (X) appear on the right and left side of the grey dot in a randomised order. The task is to ignore the + and just conduct a step as quickly as possible in the direction that an (X) appears (Figure 5).

**Figure 5 fig5:**
[figure not shown]
Display of the Go/No-Go test.

###### Inhibition and brain activity

2.4.2.1.4

The Stroop Test assesses inhibition (cognitive interference). The interference occurs when a specific stimulus is impeded by a second stimulus attribute, known as Stroop Effect (41). A computer-based version of the Stroop Colour-Word will be conducted to assess the inhibitory component of executive functioning (42–44). In compatible trials of the task, colour words are presented in the same colour (e.g., “green” printed in green), whereas in incompatible trials, colour words are presented appearing in a different colour (e.g., “yellow” printed in blue). Participants are instructed to press a button corresponding to the word meaning, ignoring the colour of ink the word is written in. Before the test, 4 examples are shown and a practice round is administered, which includes 12 trials with feedback on the response. Afterwards, compatible and incompatible trials are presented in 8 alternating blocks (with 12 trials each), which are interspersed by a recovery period. On each block, colour words are presented for 350 milliseconds (ms) on black background and responses are allowed within a 1,250 ms time window. To avoid habituation, the inter-stimulus interval varies randomly between 900 and 1,100 ms. Reaction time in ms on response-correct trials and accuracy in % is extracted separately for compatible and incompatible trials. Interference in ms is calculated as the difference in reaction time (on trials with correct responses) between compatible and incompatible trials. The Stroop Test will be coupled with a functional near-infrared spectroscopy (fNIRS) system (NIRx Medical Technologies, NIRSport2, Berlin, Germany) to assess changes in cortical haemodynamics during the cognitive test. The systems combines 8 light sources and 7 detectors, which are evenly distributed over the prefrontal cortex, resulting in 20 measurement channels. Based on neurovascular coupling, these measured changes allow conclusions on neural activity in this brain area of interest (45). Outcomes are the peak and average changes from resting baseline concentration of oxygenated (HbO2) and deoxygenated haemoglobin (HHb) during compatible and incompatible test blocks, respectively.

##### Physical functions

2.4.2.2

###### Functional mobility

2.4.2.2.1

Functional mobility will be measured using the instrumented version of the Timed Up and *Go Test (iTUG)*. The iTUG (46), is based on the “normal” TUG test developed by Podsiadlo and colleagues 1991 (47). It is an easy-to-do test that requires only a chair and a stopwatch. Four inertial sensor units (Opal, APDM, Oregon, United States) are attached to the participant’s body with elastic straps. At the start signal participants must stand up from a chair, walk 3 m at a comfortable walking speed, come back and sit down on the chair again. Time to complete the task as well as several other performance metrics from all the test’s phases (sit-to-stand transition, gait, turn and turn-to-sit transitions) are computed with the Software “Mobility Lab 2^®^; Oregon, Version 2.0.0.201903301644,” that comes along with the inertial sensor system. A dual-task condition will also be conducted. In the dual-task condition, a second (cognitive) task is added; participants have to count backwards in steps of three from a random given number between 200 and 250 while they are performing the test (“serial threes”). Following outcome measures will be used for further analyses for the single task and the dual-task conditions respectively: total duration, sit-to-stand duration, turn velocity, turn-to-sit duration. Additionally, relative dual task costs (DTC) of walking as percentage of loss relative to the single-task walking performance, according to the formula DTC [%] = 100 * (single-task score − dual-task score)/single-task score (48) will be calculated.

###### Coordination

2.4.2.2.2

Motor coordination is assessed using the 4 Step Square test (4SST). The 4SST assess a person’s ability to step as quickly as possible in all 4 directions: forward, backward and sidewards. At the start, the participant stands in Square 1, facing Square 2 and will step clockwise over every Square until Square 4 and anti-clockwise back to Square 1. Time is measured to complete this task (49).

###### Dynamic balance

2.4.2.2.3

Dynamic balance is assessed with the Shape Tracking Test. Participants are asked to move their center of pressure (COP) displacement by bending or rotating their body without moving the feet, so that they remain within the track that is shown on the screen (see Figure 6).

**Figure 6 fig6:**
[figure not shown]
Display of shape tracking test.

###### Static balance

2.4.2.2.4

*Postural Sway* will be assessed with the iSway test (50) of the APDM inertial sensor system. One inertial sensor unit (Opal, APDM, Oregon USA) is attached to the participant’s body (lower back) with an elastic strap. Participants are required to stand as still as possible for 30 s. Several center of pressure (COP) displacement measures are computed with the Software “Mobility Lab 2^®^; Oregon, Version 2.0.0.201903301644,” that comes along with the inertial sensor system. Mean displacement velocity and sway area will be used for further analyses.

###### Gait

2.4.2.2.5

Gait Analysis will be conducted with the iWalk test of the APDM inertial sensor system. Four inertial sensor units (Opal, APDM, Oregon United States) (two at the feet, one at the lower back and one on the chest) are attached to the participant’s body with elastic straps. Participants are required to walk for 2 min as fast as possible (but without running). Several gait performances metrics are computed with the software “Mobility Lab 2^®^; Oregon, Version 2.0.0.201903301644” (51), that comes along with the inertial sensor system. Stride length, stride velocity, and gait variability will be used for further analyses.

###### Leg proprioception

2.4.2.2.6

Leg proprioception will be assessed using the Dynamic Position Test of the ProMeTo-System. In this test, the examiner will move participants joints (extension or flexion) into several positions/angles. Participants will be asked to memorize and replicate exactly the position that the examiner specified without visual control. Three different joints are tested: hip, knee and ankle. The range of motion (ROM) of every joint is measured by moving the joint two times in either full internal rotation and external rotation for the hip or extension and flexion in the knee prior to the onset of the test. In the ankle joint the plantarflexion and dorsiflexion ROM will be measured. Inertial sensors (Shimmer Research Ltd., Dublin, Ireland) provide the angle difference (in degrees) between the position given by the test leader and the position imitated as accurately as possible by the participant. Average angle differences for each joint will be used for further analyses.

Because there are currently no reference values and/or standard error measurement values for this population, this test will be repeated twice before the onset of the intervention (once during the pre-assessment, together with all the rest of the pre-port assessments and once again one day later, just before starting the first training session) in order to calculate its test–retest reliability and assessment error (minimum detectable difference) for this population.

###### Balance confidence

2.4.2.2.7

The German version of the Activity-specific balance confidence scale (ABC-D) will be used to assess balance confidence in various activities in older people (52). The questionnaire uses an answer scale from 0 to 100% about the confidence of maintaining balance by activities. An answer of 0% indicates no confidence in conducting the activity and 100% suggests full confidence in performing the activity. In total 16 questions will be asked, and the total mean scores will be calculated.

###### Gait confidence

2.4.2.2.8

The German version of the Modified gait efficacy scale (mGES-D) will be used to assess perception of confidence in walking under challenging circumstances. It is a 10-item questionnaire on a 10-point Likert scale. 1 means no confidence; 10 means full confidence. 100 points means complete confidence in every task (53).

#### Demographic data

2.4.3

The following demographic data will be collected to further describe the study population: age, years of education, body weight, body height, NIH Stroke Severity Scale (54), main symptoms, time since stroke, comorbidities using the Cumulative Illness Rating Scale (CIRS) (55) and further treatments received during the intervention period.

#### Statistical analyses

2.4.4

All statistical procedures will be conducted with the IBM SPSS statistics software or R (RStudio, Boston, MA, United States). For demographics as well as training adherence and compliance, all collected data will be included (i.e., including data of dropouts up to the time point of their withdrawal). For all further analyses, only data of participants with an adherence ≥70% will be analyzed (per protocol analysis). A separate descriptive analysis of data from withdrawn participants who terminated the intervention prematurely or had to be excluded during the study or participants with adherence <70% will also be provided. Data will be reported as mean (SD) values for continuous parametric data and median (IQR) values for continuous nonparametric data. Data will be tested for normal distribution using Shapiro-Wilks Test and Q-Q-plots as well as for homogeneity of variance using Levene test. General level of significance used is established as *p* = 0.05. For the physical and cognitive tests that serve as secondary outcomes and are assessed in a pre-post manner, a two-way repeated measures ANOVA with group assignment (control vs. intervention group) as between subject factor and time-point (pre- vs. post-training) as within factor will be conducted. In case length of stay (and thus number of training sessions) vary across participants, we will conduct repeat our analyses controlling for this parameter. In order to determine the effects of the outcomes, effect sizes will be calculated for all primary and secondary outcomes. If any of the assumptions for parametric testing is not met, the non-parametric alternative (Friedman’s ANOVA) will be used. If the two-way mixed ANOVA or Friedman’s ANOVA report a significant group, time or interaction effect, data will be further analyzed using post-hoc tests. To calculate effect sizes of intragroup differences between post- and baseline measurements, a dependent T-test or its non-parametric equivalent (Wilcoxon signed rank test) will be used. The effect size will be interpreted using benchmarks describing the effect size as small (r ≥ 0.01), medium (r ≥ 0.3), or large (r ≥ 0.5) (56).

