There is currently just one study that has looked into the effects of exergame-based cognitive-motor training with the additional proprioceptive stimulation by playing the exergames on a labile platform (23). They found that compared to the training on a stable platform and to a passive control group, training on an instable platform is more effective for the improvement of reactive balance and functional mobility under dual-task conditions in healthy, community-dwelling older adults. The feasibility and effects of this type of exergame training on labile surface and thus rich in proprioceptive stimulation in stroke patients remains unknown.

Therefore, the aim of this study is to assess the feasibility and effects of exergame-based cognitive-motor training on a labile platform on physical and cognitive functioning in stroke inpatients.

We hypothesize that exergame-based cognitive-motor on a labile surface will be feasible within the context of inpatient rehabilitation of stroke patients. In addition, we hypothesize that compared to training on stable surface, training on a labile platform will be more effective for the improvement of motor and cognitive functioning in stroke inpatients.

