### Study design and procedures

2.1

The study is a pilot randomized control trial with two parallel groups; a control group and an intervention group with a 1:1 allocation ratio. The study will only be blinded on pre-measurement. Afterward group assignment blinding is no longer possible because the pre-assessments and training sessions will be carried out by the same study staff. Data collection will be carried out in the neurologic rehabilitation clinic in Zihlschlacht, Switzerland. All study procedures will be performed in accordance with the Declaration of Helsinki. The study protocol was reviewed and approved by the Cantonal Ethics Committee of Eastern Switzerland (EKOS 24/002). Any substantial amendment to the study protocol will have to be approved by the same Ethics Committees and the trial registration at clinicaltrials.gov NCT06296069 will be updated accordingly.

At clinic admission, patients potentially fulfilling the eligibility criteria will be informed in oral and written form about the study and asked if they wish to participate. All interested participants will then be screened for eligibility by the local principal investigator. The included participants will undergo the baseline assessments (T1) and will be subsequently randomly allocated to the intervention or the control group using permuted block randomization with blocks of four. Screening and baseline measurements will be conducted within the first two days upon admission. To minimize physical and cognitive fatigue, a consistent assessment sequence alternating between physical and cognitive tests will be enforced. Participants will be encouraged to ask for a break whenever needed. One day after the T1 measurements, the intervention period will begin. The intervention period will be equal to the length of the stay in the rehabilitation clinic (between 3–4 weeks, according to cantonal/regional regulations and insurance coverage). At the last two days before discharge, post-measurements (T2-measurements) will be performed with all (intervention & control) study participants. Participants will be withdrawn from the study if they develop symptoms or diseases regarded as exclusion criteria during the study.

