### Participants and eligibility

2.2

Primary outcomes of this pilot study are feasibility measures (e.g., adherence, attrition, motivation, enjoyment, adverse events) which do not require an *a priori* sample size calculation. The selected sample size is based on the recommendations of Whitehead et al. (25). Since we are aiming for a future main trial designed with 90% power and two-sided 5% significance and aim to be able to detect medium effect sizes, we will use a sample size of n = 15 per treatment arm. Therefore, 30 participants will be included in the study with 15 participants allocated to each group (intervention or control group). Inclusion criteria are: prescription for inpatient rehabilitation due to a stroke, ability to provide a signed informed consent, age ≥ 50 years, Mini Mental State Examination (MMSE) ≥ 20, ability to stand for at least 3 min without external support. Exclusion criteria are: depending on assistance for ambulation (Functional Ambulation Categories <2), insufficient knowledge of the German language to understand the instructions and games, conservatively treated osteoporotic fractures in the last 16 weeks and presence of any mobility, cognitive, sensory and/or psychiatric limitations or comorbidities which impair the ability to play the exergames and/or conduct the pre-/post assessments.

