##### Training goals

2.4.1.8

Personal goals regarding rehabilitation/training will be assessed with the Goal Attainment Scale *(GAS)*. The GAS is an individual approach to defining and evaluating personal rehabilitation goals (35, 36). The goals will be defined at the beginning of the intervention and will be reevaluated in the middle (after 8 trainings) and at the end of the intervention period. The scale consists of a five-point rating of the achievement of the specified goals. A score of 0 corresponds to the expected improvement or achievement of the predefined goal. A negative score of −1 or −2 is considered worse than expected. A positive score of 1 and 2 is given when the goal is achieved even better than expected. Interpersonal scores for the three time-points will be evaluated descriptively for each participant separately.

The feasibility of the intervention is pre-determined using the following feasibility criteria:

no intervention-related adverse events.maximum 10% attrition rate.at least 70% adherence rate.

If all three criteria are met, we deem the intervention to be feasible. If one to two criteria are not met, the intervention is feasible but needs modifications. If none of the criteria are met, the intervention will be deemed not feasible.

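### The labile-versus-stable comparison is planned only in participants with at least 70% adherence, and it is unclear whose adverse events count toward feasibility

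*Protocol article*

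**What the plan says.** All references are to the protocol article.

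- **Analysis sets (2.4.4 Statistical analyses).** One group of analyses uses everybody: "For demographics as well as training adherence and compliance, all collected data will be included". The next sentence restricts the rest: "For all further analyses, only data of participants with an adherence ≥70% will be analyzed (per protocol analysis".
- **Those left out (2.4.4).** They are not ignored. The section promises "A separate descriptive analysis of data from withdrawn participants who terminated the intervention prematurely or had to be excluded during the study", and extends this to participants below 70% adherence.
- **Between-arm test (2.4.4).** The secondary outcomes are compared by "a two-way repeated measures ANOVA with group assignment (control vs. intervention group) as between subject factor", with time as the within factor. This tests the hypothesis at the end of the Introduction that "training on a labile platform will be more effective for the improvement of motor and cognitive functioning in stroke inpatients".
- **Follow-up (2.1 Study design and procedures).** T2 measurements are planned for all study participants in both groups. The section also says: "Participants will be withdrawn from the study if they develop symptoms or diseases regarded as exclusion criteria during the study".
- **Primary outcome (2.4.1).** Feasibility includes safety, usability (SUS), training load and enjoyment. Three formal criteria close section 2.4.1.8. One is "no intervention-related adverse events"; the others concern attrition and adherence.

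**The concern.** Adherence is sessions attended divided by sessions offered (2.4.1.3), so it is known only after allocation and can be affected by it. The arms share training volume and progression rules, except that in the labile arm the damping is gradually removed (2.3). If more patients, or a different kind of patient, miss sessions on the labile platform, the two 70% subsets are no longer comparable at baseline. A group-by-time effect could then reflect who was kept rather than what the platform did. The Discussion makes a larger trial depend on a finding of effectiveness, so the comparison has consequences even in a pilot.

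Safety, SUS, enjoyment and training load are not among the named exemptions. Taken literally, they too are analysed only in patients who attended most of the training. For safety this touches a formal criterion: a patient who stops because of an intervention-related event may well fall below 70%, and nothing says that this patient's event counts.

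**Working it through.** The article gives no exclusion rate, adherence-outcome correlation or adverse-event risk. Those below are assumptions, shown over a range. The only stated figure in play is the sample size, 15 × 2 = 30, which is arithmetically consistent and not disputed.

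**1. Who is excluded.** The goal review in the middle of the intervention comes after 8 trainings (2.4.1.8), which implies about 16 sessions. Then 0.70 × 16 = 11.2, so 12 must be attended. A patient attending 11 (11/16 = 69%) is left out of the comparison, even if T2 was done.

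**2. Bias in the comparison.** Let adherence and change in outcome be jointly normal with correlation ρ, and let the lowest-adhering fraction f of an arm be excluded. The mean outcome of those kept shifts by ρ × φ(z_f)/(1 − f) SD.

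- Labile, f = 0.30: 0.348/0.70 = 0.497.
- Stable, f = 0.10: 0.1755/0.90 = 0.195.
- Difference: 0.302 × ρ, in favour of labile training when better adherers do better.

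A simulation of 40,000 trials per scenario (15 per arm, no true effect, t-test on change scores, which is equivalent to the group-by-time test) gave:

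| Excluded, labile v stable | ρ | Bias (SD) | Type I error |
|---|---|---|---|
| 30% v 10% | 0 | about 0 | 4.9% |
| 30% v 10% | 0.3 | 0.09 | 5.6% |
| 30% v 10% | 0.5 | 0.15 | 6.6% |
| 30% v 10% | 0.7 | 0.21 | 8.6% |
| 20% v 5% | 0.5 | 0.12 | 6.0% |
| 20% v 20% | 0 to 1 | about 0 | about 5% |

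The simulated biases agree with the formula (0.302 × 0.3 = 0.09; × 0.5 = 0.15; × 0.7 = 0.21).

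**3. The safety criterion.** Take the 15 labile-arm patients, a per-patient risk p of an intervention-related event, and a share q of affected patients who fall below 70% adherence. The chance of meeting the criterion in the restricted set is (1 − p(1 − q))^15.

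| p | Everyone counted (q = 0) | q = 0.5 | q = 1 |
|---|---|---|---|
| 5% | 46% | 68% | 100% |
| 10% | 21% | 46% | 100% |
| 20% | 4% | 21% | 100% |

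This applies only if the restriction does govern the criterion, which the text leaves open.

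**The case against.** **Pilot status and openness.** Efficacy is secondary, the restriction is openly labelled per protocol, and the excluded patients are described separately. This limits the damage, but a separate description does not enter the comparison, and no all-randomised result is planned beside it.

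**Differential adherence may not occur.** Sessions are supervised, damping is graded, and load is adapted session by session in both arms. The Discussion reports very high adherence with the same device in other inpatient groups. If few are excluded, or exclusion is equal in the two arms, bias is about zero. This stands: the bias is a risk, not a certainty. That earlier experience did not involve a labile surface, however.

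**Adverse events are recorded throughout (2.4.1.1), and the criterion carries no adherence filter.** So the documents do not show that events are removed, and an early stopper's event should still appear in the separate description. What remains is that the only general rule on analysis sets does not exempt safety, and no text resolves the matter.

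**Stronger readings that the documents do not support:**
- A reader might infer that the feasibility verdict is tilted through usability. SUS, enjoyment and load are not among the three formal criteria, adherence uses all collected data, and attrition counts drop-outs by definition.
- A reader might infer that SD estimates justify 15 per arm and that a main trial would be under-sized. The statement "we will use a sample size of n = 15 per treatment arm" rests on a cited recommendation, and section 2.2 mentions no SD.
- A reader might charge the rule with cutting 15 per arm to 12, from 10% attrition plus an assumed 10% below the cut-off. The 10% attrition is an acceptability limit, not a forecast, and drop-outs without T2 data are missing under any analysis set. The rule itself would cost 15 × 0.10 = 1.5 per arm.

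**Conclusion.** The point holds in a limited form. The only planned between-arm test is conditioned on a post-randomisation variable that allocation can influence, with no all-randomised analysis alongside. Under assumed exclusions of 30% v 10% and moderate correlations (0.3 to 0.7), the spurious difference is about 0.09 to 0.21 SD and the type I error 5.6% to 8.6%. A larger figure can be produced: excluding 20% from one arm only, with perfect correlation, gives 0.280/0.80 = 0.35 SD. Nothing in the article supports those conditions.

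For safety, the defect is unresolved wording. Under the literal reading, the adverse-event criterion could be met although an event occurred in a patient who stopped early. If the other two criteria were met, the conclusion would then move from feasible with modifications to feasible. SUS, enjoyment and training load share the literal restriction as listed primary outcomes, but do not decide the formal verdict.

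**What to change.** 1. **Comparison (2.4.4).** Make the main group-by-time analysis all randomised participants, as allocated, with available T2 data, whatever their adherence. Keep the 70% set as a sensitivity analysis. Participants without T2 data remain missing, so report their number and reasons by arm.
2. **Safety (2.4.1.1, 2.4.1.8, 2.4.4).** State that adverse events, including those that feed the feasibility criterion, are counted in everyone who started at least one session.
3. **User-reported outcomes.** Summarise SUS, enjoyment and training load in all who started training and have data.
4. **Withdrawal (2.1).** Leave the decision to stop training as it is. Separate it from leaving the study: such patients stay in adverse-event recording and do those T2 tests that they are able to do, unless consent is withdrawn. Some will not manage every test, since the exclusion criteria include being unable to conduct the assessments.

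The cost is a minor amendment, a few extra T2 assessments before discharge, and an effect estimate slightly diluted by patients who trained less.

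### Assumption tests on about 15 patients per arm decide, outcome by outcome, whether the group x time comparison is kept or replaced by Friedman's ANOVA, which has no between-arm factor

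*Protocol article*

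**What the plan says.** The design has two parallel arms: "30 participants will be included in the study with 15 participants allocated to each group" (section 2.2). Section 2.4.4 plans, for every physical and cognitive test measured before and after training, a two-way ANOVA with group as between-subject factor and time as within-subject factor. It then sets a gate on that model:

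- The checks: "Data will be tested for normal distribution using Shapiro-Wilks Test and Q-Q-plots as well as for homogeneity of variance using Levene test".
- The level: "General level of significance used is established as *p* = 0.05". No separate level is given for the checks.
- The consequence: "If any of the assumptions for parametric testing is not met, the non-parametric alternative (Friedman’s ANOVA) will be used".

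The section does not say whether the checks apply to raw values, change scores or residuals, whether they are run per arm and visit or pooled, or how a Q-Q plot is weighed against a test. The Introduction states the hypothesis that the secondary outcomes serve: the labile surface improves motor and cognitive function more than the stable one.

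**The concern.** The trial's own outcome data choose the model, separately for each outcome, and one unmet assumption of any kind is enough. Three things follow.

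- Several 5% checks per outcome accumulate false alarms even when nothing is wrong with the data.
- With two visits, the group x time test is a comparison of change scores between arms. If the checks are made on raw values, they examine something the test does not rely on.
- The two branches do not answer the same question. Only the group x time term tests whether one arm improves more than the other. Friedman's ANOVA ranks visits within each person and contains no arm.

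At stake is whether each secondary outcome yields an arm comparison at all, and whether closely related outcomes, such as iTUG duration and 4SST time, are reported under the same model.

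**Working it through.** The article gives no rate of switching, so there is no stated figure to reproduce.

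**Inputs from the article.** 15 per arm (2 x 15 = 30); two arms and two visits, hence four group-by-visit cells; level 0.05; any unmet assumption switches.

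**Assumed, not in the article.** Pre-post correlation 0.5-0.9 (0.7 where one value is needed); log-SD 0.2-0.5 for skewed times; a failed check means p < 0.05 in any Shapiro-Wilk or Levene test. Q-Q plots are a matter of judgement and were not modelled.

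**Step 1: approximation.** With k independent 5% checks, P(at least one fails) = 1 - 0.95^k.

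- k = 6 (four cells plus Levene at two visits): 1 - 0.95^6 = 26.5%
- k = 4 (arms pooled at each of two visits, plus two Levene): 1 - 0.95^4 = 18.5%
- k = 3 (change scores per arm plus one Levene): 1 - 0.95^3 = 14.3%
- k = 2 (pooled residuals of change plus one Levene): 1 - 0.95^2 = 9.8%

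**Step 2: simulation.** Perfectly normal data with equal variances, 15 per arm, correlation 0.5-0.9, 12,000 runs per setting.

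| What is tested | False switch |
|---|---|
| Raw values, each arm and visit | 24.5-27.3% |
| The same, median-centred Levene | 21.6-23.6% |
| Raw values, arms pooled at each visit | 16.8-19.4% |
| Change scores per arm | 14.1-14.6% |
| Pooled residuals of change | 10.1-10.4% |

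With 13 or 11 per arm, the first row becomes 24-28%.

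**Step 3: skewed times.** Lognormal data, 15 per arm, correlation 0.7, no true arm difference.

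| Log-SD | Switched, checks per cell | Switched, checks pooled per visit | Type I error of the unswitched group x time test |
|---|---|---|---|
| 0.2 | 45% | 41% | 5.3% |
| 0.3 | 61% | 58% | 4.9% |
| 0.4 | 74% | 80% | 5.2% |
| 0.5 | 86% | 91% | 4.6% |

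The group x time F equals the square of the two-sample t on change scores. The raw-value checks would therefore often discard a test whose error rate is sound.

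**Step 4: does the trigger itself distort the error rate?** The per-cell trigger was simulated with a switch to a valid rank comparison of change scores between arms. Overall type I error stayed at 4.0-5.5% for normal and lognormal data, even where more than 85% of outcomes switched. The trigger alone does not inflate type I error.

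**Step 5: where the switch actually leads.** With two visits, Friedman's test uses only the direction of each person's change. Run on both arms together, it tests change over time. Run within each arm, it gives two separate tests of change. Neither is a test of arm difference.

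**Step 6: what a fixed, baseline-adjusted comparison offers.** Assume an effect of 0.7 SD and correlation 0.7, with 15 per arm.

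- Change scores: SD = sqrt(2 x (1 - 0.7)) = 0.775; 0.7 / 0.775 = 0.90; power about 67% (28 df).
- Baseline-adjusted post value: SD = sqrt(1 - 0.7^2) = 0.714; 0.7 / 0.714 = 0.98; power about 73% (27 df, ignoring chance baseline imbalance).

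**The case against.** The strongest reply has four parts.

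- **A switch is not an error.** The rates count changes of method, not wrong conclusions, and with a valid fallback the type I error is unharmed. This stands (step 4). A reader might infer that pre-testing inflates false positives here; the calculations do not support that. The fallback named in the article is not a valid arm comparison, however, so the switch costs the answer rather than the error rate.
- **The article does not say that raw values are tested, nor that a single p-value decides.** This also stands. A plot could overrule a marginal test, and on residuals the rate is 10-15%, not about 25%. No reading that keeps the tests as a gate brings the rate to zero.
- **The authors may have meant a fallback that handles groups.** Section 2.4.4 does speak of group or interaction effects from either ANOVA. Friedman's ANOVA provides neither, so the named method cannot deliver what that sentence expects.
- **These are secondary outcomes in a 30-person pilot.** True: the feasibility verdict in section 2.4.1 rests on adverse events, attrition and adherence, without a hypothesis test. This limits the weight of the point.

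Two further readings are tempting and should not be made. Section 2.1 says "The study will only be blinded on pre-measurement", from which a reader might infer that unblinded people will judge the Q-Q plots. The article ties the loss of blinding to staff who both assess and train, and does not say who analyses the data or whether arm codes are masked. A reader might also multiply the rates into a number of outcomes lost, but the article gives no count of analysed outcomes to multiply by.

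**Conclusion.** The point holds, as a change that should be made rather than one on which the trial depends. The model for each secondary outcome is chosen by assumption tests on about 15 per arm. Applied mechanically to perfectly normal data, they switch falsely in about 25% of outcomes (raw values per arm and visit), 17-20% (raw values pooled per visit) or 10-15% (change scores or residuals). For right-skewed times, raw-value checks switch about 40-90%, under log-SDs that are assumed. The rates rest on a 0.05 cut-off for every check and leave out any judgement from Q-Q plots; correlation matters little below 0.9.

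The consequence is loss of the between-arm test for switched outcomes and inconsistent models across similar outcomes.

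**What to change.** In section 2.4.4, delete the switch driven by assumption tests and fix one analysis per outcome in advance:

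- A baseline-adjusted between-arm comparison of the post-training value.
- Log scale for strictly positive times: TMT-A, TMT-B, iTUG and 4SST durations, step reaction time.
- Raw scale for all other outcomes, including differences that can be zero or negative: TMT.B-TMT.A, Stroop interference and dual-task cost.
- One pre-specified rank or permutation comparison of the arms as sensitivity analysis for all outcomes, reported whatever the residuals look like.
- Residual plots as a diagnostic only, with no effect on which analysis is reported.

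This brings false switching to zero and gives every outcome an arm comparison. Design, sample size and data collection stay as they are. The cost is a rewording of one section, and timed outcomes are then reported as ratios between arms rather than as differences in seconds or milliseconds.
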